### Coherence analysis

2.3

Coherence analysis between pulse rate variability and blood pressure variability will be performed on 1-h ABP waveform segments. Peaks corresponding to systolic pressure of each cardiac cycle will be detected, and Gaussian filter will be applied to exclude frequencies above 10 Hz (47). Pulse rate variability and blood pressure variability will be calculated based on frequency domain analyses of the waveform derived after applying a Gaussian shape to the time differences between subsequent cardiac cycles. Power spectral density (or power spectrum) will be used to quantify the frequency content of a blood pressure variability or pulse rate variability. Coherence will be calculated using mscohere function in MATLAB (47).

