### Data analysis

2.2

Based on data from the currently recruited 550 patients, we found some incomplete ECG recordings of short duration, necessitating data analysis based solely on the ABP signal. To address this issue, we will conduct the eAD characterization on two fronts: one from both ECG and ABP waveforms, and the other from only ABP waveforms.

We will conduct non-invasive characterization of eAD by computing multiple indices over 24 h following admission, including heart rate turbulence (HRT) (18), time- and frequency-domain analyses of HRV and sequence analysis of BRS. First, we will slice the long-monitoring waveform into 1-h segments and assess the signal quality for both ECG and ABP segments. Next, the premature ventricular contractions (PVC) detection will analyze high-quality ECG segments. If more than 10 PVC beats for a given 1-h segment are detected, we will conduct HRT analysis on ECG waveforms (19). HRT is generally assessed by two parameters: turbulence onset (TO) and turbulence slope (TS). TO measures the initial acceleration and subsequent deceleration of heart rate after a PVC, while TS quantifies the rate of heart rate return to baseline. We will extract two time series from the ECG and ABP waveforms: one consisting of RR intervals from normal sinus beats, and the other comprising systolic blood pressures (sBP) from ABP pulses. We will then perform three analyses on these sequences: extracting root mean square of successive differences (RMSSD) and HRT from time-domain RR interval sequences, transforming RR intervals into the frequency domain to calculate the low- and high-frequency band ratio, and estimating BRS indices from RR intervals and sBP sequences. For eAD characterization based on ABP signals alone, we will compute autonomic indices from pulse interval sequences, excluding HRT due to the difficulty of detecting PVC beats without ECG waveforms. Figure 1 summarizes the entire procedure, with detailed explanations of each function block provided in the following sections.

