For the case of eAD characterization utilizing ABP signal alone, we will extract pulse-to-pulse interval (PPI) based on detected systolic blood pressure from high-quality ABP waveforms and calculate pulse rate variability. We identify the intervals between fiducial points in successive pulses as PPI. Based on PPI time series, we will calculate RMSSD, the ratio of LF/HF and BRS metrics in place of using RR interval time series.

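### Section 2.3, as worded, takes pulse rate variability and blood pressure variability from the same beat-timing waveform, so their coherence is 1 by identity; probably a drafting slip, of minor severity

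*Protocol article*

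**What the plan says.** Section 2.3 (Coherence analysis) sets the aim: "Coherence analysis between pulse rate variability and blood pressure variability will be performed on 1-h ABP waveform segments".

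The preparatory step is: "Peaks corresponding to systolic pressure of each cardiac cycle will be detected, and Gaussian filter will be applied to exclude frequencies above 10 Hz".

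One sentence then defines both quantities: "Pulse rate variability and blood pressure variability will be calculated based on frequency domain analyses of the waveform derived after applying a Gaussian shape". By the rest of that sentence, the waveform is built from the intervals from one beat to the next.

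The estimator is fixed last: "Coherence will be calculated using mscohere function in MATLAB". The section cites an external method paper for the peak and filter step and again for the estimator. That paper is not available here.

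Two definitions elsewhere in the article bear on the point:

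- Section 2.2.6 defines the pulse interval: "We identify the intervals between fiducial points in successive pulses as PPI". This is the same kind of timing quantity from which section 2.3 builds its waveform.
- Section 2.2 extracts two beat series from the recordings, one of intervals and "the other comprising systolic blood pressures (sBP) from ABP pulses". Section 2.2.5 then uses the low-frequency spectral density of that pressure series in its baroreflex gain (Equation 10).

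Section 2.3 refers to neither definition.

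**The concern.** Coherence describes how consistently two different signals move together at each frequency. Here one should carry beat timing and the other pressure. The defining sentence in section 2.3 names one source for both, and that source holds only times between beats. Systolic peaks are located, but the only use of them that the section states is to time the cycles. Their height in mmHg is not named as an input to anything.

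If an analyst coded the sentence as it stands, the section would return the same value for a patient with intact coupling and for one with none. The spectrum labelled blood pressure variability would be a second copy of the pulse-interval spectrum, in units of time. The article presents itself as a pre-planned protocol, and its Discussion undertakes to report deviations, so an analyst who did the sensible thing would also be departing from the text.

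**Working it through.** The plan states no figure for this analysis, so there is nothing to reproduce. The check is an identity, followed by a numerical confirmation.

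**Inputs from section 2.3**

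- Quantities to be compared: pulse rate variability and blood pressure variability, on 1-h arterial pressure segments.
- Source of both: one waveform, from "applying a Gaussian shape to the time differences between subsequent cardiac cycles".
- Estimator: magnitude-squared coherence (`mscohere`).

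**Step 1. The identity.** With x and y as the two inputs,

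`C(f) = |Pxy(f)|² / (Pxx(f) · Pyy(f))`

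- Same waveform in both places (y = x): Pxy = Pyy = Pxx, so `C = Pxx² / (Pxx · Pxx) = 1`.
- One copy linearly filtered with response H: |Pxy| = |H|·Pxx and Pyy = |H|²·Pxx, so `C = |H|²·Pxx² / (Pxx · |H|²·Pxx) = 1`.

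Smoothing, rescaling or inverting one copy therefore does not help. The value is 1 at every frequency with power, and it does not depend on window length or sampling rate.

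**Step 2. Numerical confirmation.** A 1-h beat series was simulated with a mean interval of 0.75 s, placed on a 25 Hz grid, smoothed with a Gaussian kernel, and analysed by Welch averaging with 128-s windows and 50% overlap. The bands are those of the article: LF 0.04–0.15 Hz and HF 0.15–0.4 Hz. The other settings are assumptions.

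| Inputs | LF band mean | HF band mean |
|---|---|---|
| Same interval waveform twice | 1.000 | 1.000 |
| Same waveform, one copy rescaled and inverted | 1.000 | 1.000 |
| Same waveform, one copy smoothed again | at least 0.99999 | about 0.99998 |

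These values were the same whatever coupling between pressure and interval was built into the simulated patient.

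**Step 3. With a separate pressure series.** Intervals were kept for pulse rate variability, and the simulated systolic values were used for blood pressure variability:

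| Assumed shared LF component | LF coherence |
|---|---|
| 0 | about 0.01 |
| 0.5 | about 0.24 |
| 0.9 | about 0.72 |

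The result now follows the coupling. These three values depend on the assumed settings and are not predictions for this cohort.

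**Step 4. Does anything downstream use it?** Section 3 (Statistical analysis) and section 4 (Expected results) build early autonomic dysfunction from five indices: RMSSD, HRT, BRS, LF power and LF/HF. Coherence is not one of them. The abstract's methods and the overview in section 2.2 do not list it, and no threshold or hypothesis is attached to it.

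**The case against.** The best reply is that the sentence is condensed and that the rest of the article shows what is meant. Section 2.3 names two distinct quantities and speaks of a power spectrum for either one. It detects systolic peaks, and the 10 Hz filter is most naturally a step on the pressure waveform. Section 2.2 extracts a systolic pressure series, section 2.2.5 takes the spectrum of that series, and section 2.2.6 treats oscillations in pressure and in heart rate as separate signals. The cited method paper may set out how each series is built. Nothing says outright that the same series is entered twice.

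Most of this stands as evidence of intent, and it makes a drafting slip the likeliest explanation. It does not repair the text. Section 2.3 does not leave the source of blood pressure variability open: it states one, and that source contains no pressure. It does not point to the systolic series defined elsewhere, and an unseen reference cannot be assumed to override an explicit sentence.

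Three stronger readings are tempting but are not supported:

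- A reader might infer that the investigators will in fact report a coherence of 1 for every patient. The documents do not show that, and a uniform value of 1 would be noticed on the first run.
- A reader might want to state how far a patient without coupling would be misreported. The article gives no window settings, and the level expected without coupling depends on them: simulations of unrelated series gave about 0.01, 0.05 or 0.13 under different assumed settings. No single figure can be given.
- A reader might infer that the baroreflex results or the classification of early autonomic dysfunction are compromised. Equation 10 uses the spectrum of the systolic series itself, and the article does not make any index conditional on coherence.

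**Conclusion.** The point holds for the wording of section 2.3. One timing waveform is named as the source of both inputs, so the rule as stated yields a coherence of 1 and carries no information on pressure. That conclusion is an identity and needs no assumption about windows, sampling or patients. It rests only on reading the defining sentence as written.

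The severity is minor. A slip in drafting is more likely than a planned error, the systolic pressure series needed for a correct analysis is already part of the plan, and neither the five-index definition nor the primary analysis depends on coherence.

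**What to change.** Reword the defining sentence in section 2.3 to say that:

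1. blood pressure variability is derived from the beat-to-beat systolic pressure values, in mmHg, that is, the systolic series already defined in section 2.2;
2. pulse rate variability is derived from the intervals between successive pulses, as in section 2.2.6;
3. both series are placed on a common time base before `mscohere` is applied to the pair.

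How the common time base is obtained can stay with the investigators, including whether the Gaussian construction is applied to each series separately. The cost is one or two sentences and, if the code follows the present wording, a small change to it. The systolic values are already to be detected, so no new data are needed.

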## Statistical analysis

3

The characterization of eAD requires consideration of age-specific analysis. We will stratify patients into age to account for known age-related differences in autonomic function; Within each age stratum, we will establish reference distributions based on published normative data for that specific age group; For each autonomic measure, we will use age-appropriate reference ranges from healthy controls as reported in large-scale studies. Normally, RMSSD values should fall between 19 and 75 ms (48), HRT should exhibit a turbulence onset near 0% and a turbulence slope above 2.5 ms/R-R interval (49), and BRS is around 4.87–34.07 across different age groups over 20 years old (50).

For the determination of eAD, we will quantify the incidence and magnitude of anomalies such as reduced RMSSD, HRT, and BRS, alongside increased low frequency (LF) power and an elevated LF/HF ratio, which are critical indicators. eAD will be characterized if three or more of these indicators exceed or fall below 2.5 standard deviations from age and sex-standardized values. Autonomic function measures will also be considered as continuous variables as well. For the primary analysis, we will use data from patients over their first 24 h following ICU admission to identify eAD, as well as examine the association of these measures with clinical outcomes. In exploratory analysis, we will describe autonomic function measures over the first 5 days following ICU admission.

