#### Heart rate turbulence quantification

2.2.4

HRT refers to the fluctuations of sinus heart beat cycle length caused by PVC beats (18). When a PVC beat occurs, it results in a shortened interval with the prior beats and this interval is termed coupling interval (couplI). A longer interval than that of a normal sinus beat is then followed, which is a compensatory interval (compI) (36). The HRT reflects the natural fluctuation of HR after the compI. If more than 10 beats are detected as PVC, we will conduct HRT analysis to compute turbulence onset (TO) and slope (TS) (19) for each PVC beat. TO is an indicator to reflect the vagal inhibition by quantifying the initial fast increase of heart rate (36) and calculated as Equation 6:

(6)
$$TO=\frac{\left(RR_{1}+RR_{2}\right)-\left(RR_{-2}+RR_{-1}\right)}{RR_{-2}+RR_{-1}}\times 100\%$$

where 
$RR_{1},RR_{2}$
 are two RR intervals immediately after compI, and 
$RR_{-1},RR_{-2}$
 are two RR intervals immediately preceding couplI.

TS is an indicator to reflect the vagal activation and is measured as the maximum positive regression slope over any 5 consecutive sinus rhythm RR intervals within the first 15 RR intervals after the compI (19). Therefore, the analysis for both HRT parameters will require at least 2 sinus rhythm RR intervals before couplI and at least 15 RR intervals after compI. For 1-h ECG segments, we will compute the mean of TO and TS across all detected PVCs to obtain an average value that represents the overall heart rate turbulence for the recording period.

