## Expected results

4

Quantification of individual eAD indices, defined as reduced RMSSD, reduced HRT, reduced BRS, decreased LF power, decreased LF/HF (45, 51) (less/greater than 2.5 SDs of age/sex-standardized values) measured over 24 h following admission.Quantification of eAD, defined as 3 or more (out of 5) indices less/greater than 2.5 SDs of age/sex-standardized values measured over 24 h following admission.

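### The stated normal turbulence onset conflicts with the plan's own formula, and averaging per-PVC maximum slopes inflates turbulence slope

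*Protocol article*

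**What the plan says.** Section 2.2.4 (Heart rate turbulence quantification) defines both parameters. Equation 6 is TO = [(RR1 + RR2) - (RR-2 + RR-1)] / (RR-2 + RR-1) x 100%, where the positive indices follow the compensatory interval and the negative ones precede the coupling interval. The text says TO works by "quantifying the initial fast increase of heart rate". TS is the "maximum positive regression slope over any 5 consecutive sinus rhythm RR intervals within the first 15 RR intervals after the compI".

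Both are computed for each PVC when more than 10 PVCs are found. For each 1-h segment the plan then says "we will compute the mean of TO and TS across all detected PVCs".

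Section 3 (Statistical analysis) gives the reference: "HRT should exhibit a turbulence onset near 0% and a turbulence slope above 2.5 ms/R-R interval". The rule for early autonomic dysfunction (eAD) in the same section is three or more indicators lying more than 2.5 SD from values standardized for age and sex. Section 4 (Expected results) lists the abnormal indices as "reduced RMSSD, reduced HRT, reduced BRS" together with two spectral indices, five in all.

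**The concern.** There are two separate problems.

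**Direction of TO.** The formula, its stated meaning and the stated normal value do not agree. If heart rate rises after the PVC, RR shortens and Equation 6 is negative. The reference in section 3 therefore describes a heart that does not respond. One word, reduced, is then applied to an index with two parameters that move in opposite directions when turbulence is blunted. An analyst coding from this text has no consistent instruction for TO.

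**Order of averaging for TS.** The maximum of several noisy slopes is positive even when the true slope is zero. Averaging many such maxima makes the estimate more precise but leaves its bias unchanged. A patient with no turbulence can therefore show a TS that looks preserved.

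HRT is one of the five eAD indices, and the Discussion puts its use in this population first among the study's novel aspects. The eAD classification over the first 24 h belongs to the primary analysis.

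**Working it through.** **1. TO, from Equation 6**

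The RR values are illustrative.

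- No change, 700 to 700 ms: (1400 - 1400)/1400 = 0%.
- Acceleration, 700 to 680 ms: (1360 - 1400)/1400 = -2.9%.
- Deceleration, 800 to 808 ms: (1616 - 1600)/1600 = +1.0%.

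A preserved response lies below zero, and its absence lies at zero. The reference in section 3 gives the second as normal. A numerically reduced TO is a more negative one, which is a stronger response. For TS a reduced value is a weaker response.

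**2. TS with no turbulence present**

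Inputs from the article:
- 15 RR intervals and 5-beat windows, so 15 - 5 + 1 = 11 overlapping slopes;
- at least 11 PVCs;
- normal RMSSD 19 to 75 ms (section 3).

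Assumed, because the article gives no noise model: Gaussian white noise around a flat RR sequence, for which SD = RMSSD/√2.

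Each slope is Σ(x·RR)/10 with x = -2, -1, 0, 1, 2. In simulation the expected maximum of the 11 slopes is 0.496 x SD, which is 0.35 x RMSSD. The number of PVCs does not enter this expectation when maxima are averaged. If the RR sequences are averaged over K PVCs first, the noise SD falls by √K, and with K = 11 the factor becomes 0.496/√11 = 0.149 x SD.

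Simulated results with K = 11 and zero true turbulence:

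| RMSSD (ms) | Per-PVC TS, then mean | P(TS < 2.5) | RR averaged first | P(TS < 2.5) |
|---|---|---|---|---|
| 5 | 1.76 | 1.000 | 0.53 | 1.000 |
| 7 | 2.45 | 0.582 | 0.74 | 1.000 |
| 8 | 2.80 | 0.159 | 0.84 | 1.000 |
| 10 | 3.51 | 0.002 | 1.06 | 0.999 |
| 19 | 6.67 | 0.000 | 2.01 | 0.768 |
| 30 | 10.53 | 0.000 | 3.17 | 0.299 |
| 75 | 26.32 | 0.000 | 7.94 | 0.010 |

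**3. Where noise alone reaches 2.5 ms/RR**

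- Per-PVC averaging: SD = 2.5/0.496 = 5.04 ms, so RMSSD = 5.04 x √2 = 7.1 ms, whatever K is.
- RR averaged first: 7.13 x √K, which is 23.7 ms for K = 11, 31.9 ms for K = 20 and 50.4 ms for K = 50.

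**4. Sensitivity of the per-PVC crossing to the noise model**

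- AR(1) with correlation -0.3 to 0.9: RMSSD 9.1 down to 4.0 ms.
- Random-phase respiratory sinusoid with a period of 4 to 8 beats: RMSSD 13.9 down to 2.6 ms.

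The upward bias appears under every model. Its size depends on the model.

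**The case against.** The strongest reply is that 0% and 2.5 ms/RR are not the decision rule. Section 3 gives them as descriptive normal values, and eAD is flagged at 2.5 SD from standardized values in either direction. If the norms actually used centre on a negative TO, a blunted TO deviates upward and the rule can catch it. Reduced HRT can also be read as a weaker response, so the text does not prove that the wrong tail will be flagged. This stands. It leaves the conflict between the reference and Equation 6 in place, and the abnormal direction of each parameter unstated.

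On TS, the noise structure is assumed, and low background variability is plausible here: section 1.1 links refractory intracranial hypertension with reduced heart rate variability. Under white noise with RMSSD of 6 ms or less, a patient without turbulence falls below 2.5 with probability 0.95 or more. Norms built by the same per-PVC method would absorb part of the bias. Both points stand and limit the size of the problem.

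It is also fair that HRT is one of five indices of which three are needed, requires more than 10 PVCs in a segment, and is left out of the ABP-only analysis. The measures are also to be considered as continuous variables. The effect on the number of patients classified with eAD is therefore unknown.

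A reader might infer that the HRT index cannot detect blunted turbulence at all, or that healthy TO responses will be flagged as abnormal. The document supports neither. The first fails at low RMSSD and overlooks the 2.5-SD rule. The second needs a normative mean and SD for TO that the article does not give.

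**Conclusion.** The point on TO holds from the article alone: the stated normal value is the one Equation 6 returns when turbulence is absent, and one direction of abnormality is given for two parameters that blunt in opposite directions.

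The point on TS holds in direction and, conditionally, in size. Across the article's own normal RMSSD range, noise alone gives a mean TS of about 7 to 26 ms/RR under white noise, so blunted TS tends to be missed against 2.5 unless RMSSD is already very low (below about 7 ms, or about 3 to 14 ms across the models tried). Under white noise the noise part of TS is proportional to RMSSD, so TS also partly repeats another of the five indices.

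How much of this passes into the 2.5-SD flag cannot be determined, because the article does not show how the published TS norms were computed. If they came from averaged RR sequences, the bias enters directly.

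**What to change.** 1. In section 3, correct the TO reference so that the normal response is negative, in line with Equation 6.
2. Keep the 2.5-SD rule, but state the direction for each parameter: TO abnormal when too high, TS abnormal when too low. State how the two form one HRT indicator. The choice of combination is the sponsor's, provided it is fixed before analysis.
3. In section 2.2.4, compute TS on the RR sequence averaged across eligible PVCs, either per 1-h segment or pooled over the 24 h. Alternatively, keep per-PVC averaging and use norms built by that same method. In either case, say how the norms were computed.
4. Acknowledge that averaging first reduces the bias without removing it when RMSSD is high and PVCs are few: with 11 PVCs and RMSSD 30 ms, the noise-only mean is still 3.17. Report the number of PVCs behind each TS.

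Fixed cut-offs in place of the standardized rule, or a single TS per patient, are not needed to solve the problem and would change the design. The cost is some rewording and a few lines of code, with no new data.

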The relationship between intracranial pressure (ICP), autonomic function, and hemodynamics in TBI follows distinct temporal patterns. In the acute phase, elevated ICP triggers an intense sympathetic response with increased catecholamine release, leading to systemic vasoconstriction and hypertension (13). This response can become particularly problematic in cases of refractory intracranial hypertension. As demonstrated in (14), refractory ICP elevations are associated with a marked dysregulation of autonomic function, characterized by persistent sympathetic hyperactivation, reduced heart rate variability, impaired baroreflex sensitivity and development of refractory arterial hypertension. These autonomic alterations can persist even after ICP normalization, suggesting a more complex pathophysiology than previously recognized. In the subacute phase, this initial sympathetic surge may be followed by autonomic exhaustion, leading to vasodilation and hypotension. Understanding these temporal patterns and their relationship to autonomic dysfunction is crucial for appropriate hemodynamic management in TBI patients.

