## Discussion

5

This study’s novelty lies not in the development of new autonomic measures, but rather in three key aspects: (1) the first application of HRT analysis in sTBI patients, providing new insights into post-ectopic beat autonomic regulation in this population; (2) the comprehensive integration of multiple autonomic measures in a large cohort of sTBI patients, allowing for robust characterization of autonomic dysfunction patterns specific to this population; and (3) the potential to establish normative values and clinical thresholds for autonomic measures in acute sTBI, which are currently lacking. This approach will provide clinicians with a more complete understanding of autonomic dysfunction in sTBI and its relationship to clinical outcomes.

Following sTBI, eAD is a complex and multifaceted issue that can significantly impact a patient’s overall health and recovery. Characterizing eAD is crucial for risk assessment, customizing pharmacological interventions, and assessing rehabilitation strategies. While small studies indicate that eAD is associated with poor outcomes following sTBI, the duration and full trajectory of eAD has been poorly characterized. This protocol outlines the data analysis procedure for quantifying acute autonomic dysfunction using cardiac telemetry waveforms. We will collect and annotate waveform data from 550 patients in a clinical trial and quantify the incidence and magnitude of eAD indices after the first day of admission. We will characterize eAD as the presence of 3 or more indices less/greater than 2.5 SDs of age/sex-standardized values measured over 24 h following admission.

In some patients, simultaneous ECG and ABP signals may be unavailable. To solve this problem, we will divide the collected data into subgroups with and without ECG information and examine eAD within both subgroups. We will report results of the planned study in one or multiple scientific papers in international peer-reviewed journals. We will note and deviations from this protocol, if any occur, in these publications.

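### The Statistical analysis and Expected results sections give opposite directions for LF power and LF/HF, two of the five components of the eAD rule

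*Protocol article*

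**What the plan says.** Section 3 (Statistical analysis) names five indicators and gives each a direction: "reduced RMSSD, HRT, and BRS, alongside increased low frequency (LF) power and an elevated LF/HF ratio". The rule follows: "eAD will be characterized if three or more of these indicators exceed or fall below 2.5 standard deviations from age and sex-standardized values".

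Section 4 (Expected results) defines the individual indices as "reduced RMSSD, reduced HRT, reduced BRS, decreased LF power, decreased LF/HF" and the composite as "defined as 3 or more (out of 5) indices less/greater than 2.5 SDs of age/sex-standardized values".

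Section 5 (Discussion) restates the composite with no direction for any index: "We will characterize eAD as the presence of 3 or more indices less/greater than 2.5 SDs of age/sex-standardized values measured over 24 h".

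The classification belongs to the main analysis: "For the primary analysis, we will use data from patients over their first 24 h following ICU admission to identify eAD". The same sentence in Section 3 adds the association of the measures with clinical outcomes, and the sentence before it says that the measures will also be treated as continuous.

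The three places agree on the 2.5 SD cut, on the minimum of three and on the 24-hour window. Sections 3 and 4 also agree that RMSSD, HRT and BRS count when reduced. They disagree on LF power and LF/HF, and nothing in the article reconciles them.

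**The concern.** Two of the five components have a sign that depends on which section the analyst follows. Whether a patient has eAD, and so how often eAD occurs, is then not a single defined quantity. Both texts are current and both state a direction, so this is neither condensation nor a detail left to a separate analysis plan.

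Timing matters as well. Sections 2.1 and 2.2 report 550 patients enrolled and some recordings already inspected for completeness. As long as the direction is open, it could be settled after results are known, and the article offers no text that would rule this out.

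**Working it through.** **Inputs.** Directions from Sections 3 and 4; threshold of at least three indices from Sections 3, 4 and 5. The article states no figure for eAD incidence, so there is none to reproduce.

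**Step 1: individual patterns.** Count the indices that deviate beyond 2.5 SD in the direction listed. Indices not named are within range.

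| Pattern | Section 3 | Section 4 | Either direction counts |
|---|---|---|---|
| RMSSD, BRS, LF power and LF/HF low; HRT not available | 2, negative | 4, positive | 4, positive |
| RMSSD low; LF power and LF/HF high | 3, positive | 1, negative | 3, positive |
| RMSSD and BRS low; LF/HF high | 3, positive | 2, negative | 3, positive |

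**Step 2: all patterns.** Let each index be low, normal or high, which gives 3^5 = 243 patterns. Let r be the number of reduced indices among RMSSD, HRT and BRS. The number of ways to obtain r is C(3,r) × 2^(3−r): 8, 12, 6 and 1 for r = 0, 1, 2, 3. LF power and LF/HF together have 9 combinations.

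- Positive under both sections: r = 3 with any LF combination, 1 × 9 = 9; r = 2 with one LF index high and the other low, 6 × 2 = 12. Total 21.
- Positive under Section 3 only: r = 2 with at least one LF index high and none low, 6 × 3 = 18; r = 1 with both high, 12 × 1 = 12. Total 30.
- Positive under Section 4 only: by symmetry, 30.

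Each section therefore classes 21 + 30 = 51 patterns as positive, and 30 + 30 = 60 of 243 are discordant. If RMSSD, HRT and BRS are allowed only to be reduced or normal, there are 2^3 × 9 = 72 patterns. The ways for r = 1 and r = 2 are then 3 each, and the discordant patterns number 3 × 2 + 3 × 6 = 24. These are counts of patterns, not proportions of patients.

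**Step 3: HRT not computable.** Section 2.2 requires more than 10 PVCs in a 1-h segment for HRT and excludes HRT for ABP-only data. If the minimum of three is kept, RMSSD and BRS supply at most two, so every eAD-positive result needs at least one of the disputed indices. With four indices, the ways for r = 2 and r = 1 are 1 and 2 × 2 = 4.

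- Positive under both sections: 1 × 2 = 2 patterns.
- Positive under one section only: 1 × 3 + 4 × 1 = 7 patterns for each section.

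So only 2 of each section's 9 positive patterns are shared. For ABP-only data, Section 2.2.6 names RMSSD, LF/HF and BRS. If only those three are used, all three must be abnormal, and no patient can be positive under both sections.

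**Step 4: two-sided reading.** If any deviation counts, the listed directions drop out and the sections agree on every pattern. Positives are C(5,3) × 2^3 + C(5,4) × 2^4 + 2^5 = 80 + 80 + 32 = 192 of 243.

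**The case against.** The strongest reply is that the threshold is worded both ways: "three or more of these indicators exceed or fall below 2.5 standard deviations" in Section 3, with similar wording in Sections 4 and 5. Read as two-sided, the rule gives the same class under every section. This reading is possible, so the class switch has to be stated as conditional on applying the listed directions. It does not remove the problem. It makes every stated direction redundant, and it counts abnormally high RMSSD or BRS as eAD although both sections say reduced.

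Three stronger readings are tempting and are not supported.

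- A reader might claim both that patients switch class and that the rule doubles the per-index false-flag rate (under normality, from 0.62% in one tail to 1.24% in two). The first needs the directions to apply and the second needs them not to, so they cannot both hold. The normal tail is also not the error rate of a three-of-five rule.
- A reader might infer that decreased is the intended direction, because Section 1.1 speaks of "reduced heart rate variability, impaired baroreflex sensitivity and development of refractory arterial hypertension". That passage does not mention LF power or LF/HF, and its list also includes persistent sympathetic overactivity. Section 1.2 says that LF and LF/HF were formerly read as sympathetic markers and are now understood as mixed. Lower overall variability does not fix the sign of a ratio. Section 4 cannot break the tie, because it is one of the two conflicting texts.
- A reader might conclude that the whole primary analysis is undefined. The outcome association in Section 3 refers to the measures, which are also analysed as continuous variables, and those analyses do not depend on which direction is flagged.

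**Conclusion.** The contradiction stands on the wording alone. If the listed directions are applied, 60 of 243 patterns change class, and where HRT is missing every positive result depends on at least one disputed index. If the rule is two-sided, the sections agree, at the price of contradicting the word reduced for RMSSD and BRS. The article therefore supports three different rules and does not say which one applies.

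The eAD classification and its incidence are exposed, and so is any outcome analysis that uses the classification. How many patients are affected is unknown, because the article gives no joint distribution of the indices. The step without HRT assumes that the minimum of three is not lowered when an index is missing. The documents do not settle which direction is intended, and nothing in them shows that a direction has been chosen in the light of results. The point should be fixed before analysis.

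**What to change.** Before any index is compared with outcomes, reconcile the Statistical analysis, Expected results and Discussion sections. For each of the five indices, the sponsor should state and justify the one direction that counts, or say explicitly that the index is two-sided, and use identical wording in all three places. Report the alternative direction for LF power and LF/HF as a labelled sensitivity analysis.

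The cost is protocol wording and one sensitivity table. No additional data are needed. Once a single direction per index is used throughout, the discordant patterns fall from 60 of 243 to 0.
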